### Sample size

The sample size was calculated using G*Power 3.1.9.4 software, based on the primary outcome of wound area reduction [25]. A repeated-measures ANOVA (F-test) was used to account for the interaction between within-subject factors (three time points: baseline, 5 weeks, and 10 weeks) and between-subject factors (three groups: CG, G1, and G2). The analysis considered a statistical power of 0.90, an alpha level of 0.05, and an effect size of 0.31. Based on these parameters, a total sample size of 93 participants was estimated. Assuming a 10% loss to follow-up, 102 volunteers will be recruited (34 volunteers per group).

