### Statistical analysis

All statistical analyses will be conducted according to the intention-to-treat principle. Data will be tabulated in spreadsheets (Excel package) and analyzed using SPSS version 29 (Statistical Package for the Social Sciences). Sociodemographic data will be presented as descriptive statistics, absolute values and percentages, or mean and standard deviation (median and interquartile range). Normality will be assessed using the Kolmogorov–Smirnov test. The chi-square test will be applied for categorical data. To analyze differences between groups, a one-way ANOVA or the Kruskal–Wallis test will be performed. Intragroup analysis will be conducted using one-way repeated-measures ANOVA or the Friedman test. Statistical significance will be set at *p* < 0.05, and results will be presented in tables. The cumulative proportion of responders will be calculated considering a 50% healing rate, based on the article previously published by the group, and analyzed as described by Farrar et al. [22, 31]. In studies with graded outcomes, the mean difference between the curves of two groups represents the absolute risk reduction (ARR), from which the number needed to treat (NNT = 1/ARR) can be derived.

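### The 93 participants and 90% power do not follow from the stated inputs for the group-by-time interaction, and three sections disagree on the primary test

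*Protocol article*

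**What the plan says.** Protocol article, Sample size: "The sample size was calculated using G*Power 3.1.9.4 software, based on the primary outcome of wound area reduction". A repeated-measures F-test was used "to account for the interaction between within-subject factors (three time points: baseline, 5 weeks, and 10 weeks) and between-subject factors", the latter being "three groups: CG, G1, and G2". The inputs are "a statistical power of 0.90, an alpha level of 0.05, and an effect size of 0.31". The result is "Based on these parameters, a total sample size of 93 participants was estimated". Then: "Assuming a 10% loss to follow-up, 102 volunteers will be recruited (34 volunteers per group").

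Primary outcome: the variable is percentage change in ulcer area from the initial value, measured at baseline, week 5 and week 10. The section says it will be compared between groups and over time by a repeated-measures analysis.

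Statistical analysis: "To analyze differences between groups, a one-way ANOVA or the Kruskal–Wallis test will be performed". Repeated-measures ANOVA or the Friedman test appears there only for comparisons within a group.

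**The concern.** A stated sample size should follow from the stated test and inputs, and the sized test should be the one that is run. Neither can be confirmed here. The inputs do not give 93 for an interaction at usual settings, and the section that lists the tests contains no interaction.

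The 90% power is the design's main assurance about the primary outcome. If it belongs to a different test from the one reported, a non-significant result would be credited with more weight than the comparison can bear.

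**Working it through.** **Inputs from the Sample size section.** k = 3 groups, m = 3 visits, effect size 0.31 (read as Cohen's f, so f² = 0.0961), alpha 0.05, power 0.90, N = 93, 10% loss, 102 recruited.

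**Assumed, because not stated.** Correlation between visits ρ = 0.5 and sphericity ε = 1, both varied below. Power comes from the noncentral F distribution with noncentrality λ. N moves in multiples of 3.

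**1. Which test returns 93?**

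- *Between factors* (group means averaged over the three visits): λ = f²·N·m / (1 + (m − 1)ρ), df 2 and N − 3. At N = 93, λ = 0.0961 × 93 × 3 / 2 = 13.41 and power is 0.907. At N = 90 power is 0.897. So 93 is the smallest equal-arm size reaching 0.90, which matches the plan's figure.
- *Group-by-time interaction*: λ = f²·N·m·ε / (1 − ρ), df 4ε and 2(N − 3)ε. At N = 30, λ = 0.0961 × 30 × 3 / 0.5 = 17.30 and power is 0.909. At N = 27 power is 0.869. So 30 is enough, and at N = 93 power exceeds 0.999.

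| ρ (ε = 1) | N, between factors | N, interaction |
|---|---|---|
| 0 | 48 | 57 |
| 0.3 | 75 | 42 |
| 0.5 | 93 | 30 |
| 0.7 | 111 | 21 |
| 0.9 | 126 | 9 |

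- *Interaction under other effect-size conventions*, ε = 1: the SPSS convention, λ = 2f²(N − 3), needs 87. The Cohen convention, λ = 2f²N, needs 84.
- *Interaction settings that do return 93*: SPSS convention with ε = 0.9 (power 0.904), Cohen convention with ε = 0.85 (0.902), or the default convention with ρ = 0 and ε = 0.5 (0.907). None is stated.

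**2. Does the between-factors test suit this outcome?** It averages over baseline. Randomised groups do not differ systematically there, and percentage change is zero there by definition. If f is 0.31 at weeks 5 and 10 and zero at baseline, the average is 0.31 × 2/3 = 0.207. Power at N = 93 is then 0.57 (0.67 at ρ = 0.3, 0.49 at ρ = 0.7).

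**3. One-way ANOVA, as in the Statistical analysis section.** λ = f²·N, df 2 and N − 3.

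- If 0.31 is the single-visit (week-10) effect: λ = 0.0961 × 93 = 8.94 and power is 0.753 at N = 93. It is 0.794 at N = 102 with no loss. Reaching 0.90 takes N = 135. At N = 93 the f detectable with 90% power is about 0.375.
- If 0.31 is the average over three visits with no baseline difference: the week-10 f is 0.31 × 3/2 = 0.465 if the full effect is present by week 5, or 0.31 / 0.5 = 0.62 if it grows linearly. Power at N = 93 is then 0.983 or above 0.999.

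**4. Loss allowance.** 93 / 0.9 = 103.3, so 104, or 105 for equal arms. 102 × 0.9 = 91.8. Keeping 93 out of 102 tolerates a loss of 1 − 93/102 = 8.8%.

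**The case against.** **The primary outcome does have a repeated-measures plan.** The Primary outcome section says so, and the one-way line in the Statistical analysis section is general and not tied to that outcome. This stands. A reader might infer that the trial will not run any test of the kind it sized; the article does not support that. What it shows is a conflict between sections.

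**The wrong program option is not proved.** A reader might infer that the between-factors option was chosen by mistake. The match depends on ρ = 0.5, which is as unstated as the interaction settings that also give 93. This stands too: the coincidence is suggestive, no more. The ρ = 0, ε = 0.5 route is hard to defend, because a uniform correlation of zero implies ε = 1. The other two routes are possible.

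**The true power may not be 75%.** That figure needs 0.31 to be the week-10 effect. If 93 did come from the between-factors option, 0.31 is a visit average, and week-10 power is about 0.98 or higher. This stands, so 75% can only be given conditionally.

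**An article may omit ρ and ε.** Their absence alone is no fault. The fault is that the named test and the inputs that are given do not lead to the stated N at usual settings.

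**The loss shortfall is small.** Agreed: under the between-factors test power is still 0.904 at N = 92.

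**Conclusion.** The point holds in this form: 93 participants at 90% power is not reproducible for the stated interaction from the stated inputs at usual settings (30 at ρ = 0.5; 57 down to 9 for ρ from 0 to 0.9; 84 to 87 under other conventions), and the Sample size, Primary outcome and Statistical analysis sections do not agree on one primary test.

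How far actual power departs from 0.90 cannot be settled from the article. For a one-way week-10 comparison at N = 93 it is about 0.75 if 0.31 is the single-visit effect, and about 0.98 or higher if 0.31 is the visit average. A flat statement that the trial has 75% power would go too far, and so would reliance on the stated 90%. All figures read 0.31 as Cohen's f.

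The loss allowance is a minor separate slip that needs no assumption about the test: 102 with 10% loss leaves about 92, not 93.

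**What to change.** Name one primary between-group test, in the same terms, in Sample size, Primary outcome and Statistical analysis. A week-10 comparison adjusted for baseline area is one suitable choice, but not the only one. A repeated-measures model with a stated group-by-time contrast would also resolve the conflict.

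Say what the 0.31 measures: a single-visit difference, a visit average or an interaction, and under which convention.

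Keeping 102 participants, restate the power or the detectable effect for that test, giving the G*Power option, correlation and epsilon used. For an unadjusted one-way week-10 test at N = 93, that would be power of about 0.75 at f = 0.31, or a detectable f of about 0.375 at 90%.

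State that 102 tolerates 8.8% loss if 93 are to remain, or that 10% loss leaves about 92.

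The cost is rewording in three sections and possibly a less favourable stated power. No additional participants are required.

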### Eligibility criteria

One hundred and two volunteers will be recruited through the Integrated Center for Medical Specialties (CIEM) – Polyclinic, after a detailed clinical examination of the feet. The inclusion criteria are as follows: volunteers of both sexes, aged 18 years or older, with a medical diagnosis of type 2 diabetes and diabetic ulcers located on the lower limbs. Volunteers presenting signs of infection, osteomyelitis, ischemia, inability to attend the scheduled number of sessions, use of advanced ointments or dressings, and/or any contraindication to the proposed therapeutic methods will be excluded. Written informed consent will be obtained from all eligible participants, according to the inclusion and exclusion criteria, before the start of study recruitment.

### Randomization, allocation, and blinding

Participants will be assigned to one of three groups through an online randomization program [26]: G1 (*Terminalia fagifolia* Mart + wound occlusion), G2 (GaAs 904, 10 J/cm^2^ + *Terminalia fagifolia* Mart. + wound occlusion) and the control group (CG) will use Endophoton KLD (GaAs 904) with a dose of 10 J/cm^2^ + conventional dressing (Fig. 1). An independent researcher, not involved in participant care or outcome assessment, will be responsible for conducting the randomization process. Records and treatments will be placed in opaque, sealed envelopes. The study will adopt a single-blind design, in which the assessor will remain blind to the intervention received by each group until the conclusion of the clinical trial.

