### University of Texas rankings

To identify changes in ulcer depth, ulcer images will be obtained before the intervention (baseline), after 5 weeks (10 sessions), and after 10 weeks (20 sessions), and classified using the University of Texas Wound Classification System [32]. Volunteers will be grouped into A1 and C1 (superficial ulcers), A2 and C2 (ulcers involving the tendon or joint capsule), and A3 (ulcers involving the bone). This classification will be used for longitudinal assessment of ulcer depth and compared between groups over time.

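### Ulcer depth is graded at baseline, but no named comparison of area reduction adjusts for it, so some precision is given up

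*Protocol article*

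**What the plan says.** - *Eligibility criteria* excludes infection, osteomyelitis and ischemia but sets no limit on ulcer depth.
- *University of Texas rankings* has each ulcer graded from images before treatment and at 5 and 10 weeks. The groups start with superficial ulcers and continue to "A2 and C2 (ulcers involving the tendon or joint capsule), and A3 (ulcers involving the bone"). The grade's only stated use is to follow depth over time and compare it between groups.
- *Primary outcome* defines the outcome as percentage change from the ulcer's own initial area, compared between groups and over time by a repeated-measures analysis. No covariate is named.
- *Statistical analysis* states: "To analyze differences between groups, a one-way ANOVA or the Kruskal–Wallis test will be performed". Neither test has room for a covariate.
- *Randomization, allocation, and blinding* states: "Participants will be assigned to one of three groups through an online randomization program". It adds an independent researcher and sealed envelopes, and is silent on strata and blocks.
- *Sample size* states "The analysis considered a statistical power of 0.90, an alpha level of 0.05, and an effect size of 0.31", giving 93 evaluable participants, and then "Assuming a 10% loss to follow-up, 102 volunteers will be recruited (34 volunteers per group").

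**The concern.** The outcome is scaled to each ulcer's starting area, which deals with initial size but not with depth. If depth predicts how much area an ulcer loses, the spread between shallow and deep ulcers stays in the error term of every comparison named. The hypothesis needs the combination arm to do better than each single therapy, so it rests on contrasts between arms of about 31 evaluable patients, where precision is scarce. The variable that would recover some of it is already collected before treatment. Naming it now also matters: an adjustment added after a depth imbalance has been seen is open to challenge.

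**Working it through.** **Inputs from the article:** f = 0.31, alpha 0.05, power 0.90, three groups, three time points, 93 evaluable (31 per arm), 102 randomised (34 per arm).

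**Inputs assumed, because the article gives none:** correlation between repeated measures 0.5; share of deeper-than-superficial ulcers p = 20–50%; depth effect b = 0.5–1.0 within-depth SD.

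**1. The article's sample size.** With the between-groups form of the repeated-measures F-test, λ = f²·N·m / (1 + (m − 1)ρ). At N = 93 this is 0.0961 × 93 × 3 / 2 = 13.4 on 2 and 90 df, power 0.907. The smallest N reaching 0.90 is 91, which rounds up to 93 in equal groups. So 93 is reproduced and serves as the reference below. (The group-by-time interaction that the section names does not give 93: it gives 30 under the software's default option at ρ = 0.5, and 84 or 87 under the two other effect-size options. That is a separate matter.)

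**2. Variance that depth could explain.** R² = b²p(1 − p) / (1 + b²p(1 − p)).
- b = 0.5, p = 0.2: 0.04 / 1.04 = 0.038.
- b = 1.0, p = 0.5: 0.25 / 1.25 = 0.20.

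A working range of 0.05–0.20 follows.

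**3. Gain from adjustment at N = 93.** The standard error is multiplied by √(1 − R²), the N for equal precision is 93(1 − R²) rounded up, and power uses f²/(1 − R²) on 2 and 89 df.

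| R² | SE relative to unadjusted | N for equal precision | Patients saved | Power, between-groups repeated-measures test | Power, one-way ANOVA |
|---|---|---|---|---|---|
| 0 (unadjusted) | 1.00 | 93 | – | 0.907 | 0.753 |
| 0.05 | 0.97 | 89 | 4 | 0.921 | 0.775 |
| 0.10 | 0.95 | 84 | 9 | 0.935 | 0.798 |
| 0.20 | 0.89 | 75 | 18 | 0.959 | 0.846 |

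**4. Chance imbalance if allocation is not stratified.** The SD of the difference in deep-ulcer share between two arms is √(2p(1 − p)/n). At n = 31 this is 10.2 points (p = 0.2) to 12.7 points (p = 0.5). By simulation, the largest gap among the three arms reaches 20 points in 10–22% of trials at 31 per arm, and in 12–25% at 34 per arm. A 20-point gap shifts a pairwise contrast by 0.2b, that is 0.10–0.20 SD, against a standard error of √(2/31) = 0.254 SD.

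**5. Error rate of the unadjusted one-way ANOVA, simulated with no treatment effect.**

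| Scenario | All randomisations | Largest gap ≥ 20 points | Otherwise |
|---|---|---|---|
| p = 0.3, b = 0.8 | 0.050 | 0.083 | 0.043 |
| p = 0.5, b = 1.0 | 0.051 | 0.096 | 0.038 |

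The test holds its level overall. The excess appears only when a large gap has occurred, and is offset by a lower rate when it has not.

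**The case against.** A reader might infer that randomisation is unstratified and that chance imbalance in depth will therefore be taken for a treatment effect. The documents support neither step. The allocation section is silent on strata, and a condensed article often leaves strata and blocks to the full protocol. Table 3 lists allocation before the baseline depth grading, which suggests that this grade is not a stratification factor, but that is suggestive only. Nor is there a bias in the design: step 5 shows that the unadjusted test keeps its 5% level, so the risk is conditional on a realised imbalance.

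Three further objections carry weight.
- No figure in the article links depth to percentage area reduction, so the gain could be negligible.
- The depth groups are listed for an outcome scale and do not show how many deep ulcers will be enrolled. The exclusions of infection, osteomyelitis and ischemia may narrow the range.
- The repeated-measures analysis in *Primary outcome* could take a covariate and does not rule one out, so a fuller analysis plan may already include one.

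These limit the size and certainty of the point. They do not remove it, because the between-group tests that *Statistical analysis* does fix cannot use the baseline grade.

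**Conclusion.** The point holds as one about precision in the analysis, not as a defect in randomisation. The trial collects a plausible prognostic variable before treatment, and the tests it names for area reduction leave it out. If depth explains 5–20% of outcome variance, the standard error is about 3–11% larger than it needs to be, equivalent to about 4–18 of 93 patients. Adjustment would also guard against a 20-point depth gap between arms, which under unstratified allocation and a deep share of 20–50% would occur in roughly one trial in ten to one in four. All of this rests on the assumed share of deeper ulcers and the assumed link between depth and area reduction. If the link is weak, little is gained and almost nothing is lost.

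**What to change.** Pre-specify baseline depth group (superficial versus deeper, with sparse grades collapsed) as a factor in the repeated-measures comparison of area reduction that *Primary outcome* already names, and make that the between-group analysis in *Statistical analysis* in place of the unadjusted one-way ANOVA or Kruskal–Wallis test. Use the pre-treatment grade only.

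The cost is one error degree of freedom (90 to 89) and the replacement of the named tests. No additional patients, visits or measurements are needed.

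It would also help to say whether allocation is stratified. Stratifying by depth is optional: it would require grading before the envelope is opened, and without the model term it would not recover the precision. If allocation has begun, keep the list and add only the model term.

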**Fig. 1 Fig1:**
[figure not shown]
Flowchart with participant flow based on the CONSORT model. G1: *Terminalia fagifolia* Mart + wound occlusion; G2: GaAs 904, 10 J/cm^2^ + *Terminalia fagifolia* Mart.; CG: 904 nm PBM (energy density 10 J/cm^2^) + conventional curative

### Initial assessment

After meeting the eligibility criteria and signing the informed consent form, participants will have their lower limbs assessed by an external evaluator. A form developed by the researcher will be used to collect data such as personal information, clinical history, capillary blood glucose, body mass index (BMI), time since DM diagnosis, and ulcer duration. In addition, the exact affected area will be identified and recorded during the assessment.

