# Effects of *Terminalia fagifolia* mart. extract combined with photobiomodulation on diabetic foot ulcers: protocol for a randomized single-blind clinical trial

**DOI:** 10.1007/s10103-026-04963-9

**Published:** 2026-07-25

**Keywords:** Diabetic foot ulcer, Chronic wounds, Low-level laser therapy, Phytotherapy, Ulcer healing

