### Primary outcome

#### Ulcer reduction rate

The primary variable will be the rate of ulcer size reduction over 10 weeks. After the initial assessment, the DFUs will be identified, and the area will be photographed alongside a paper ruler, which will serve as a calibrator for the ImageJ software (Fig. 2) [28, 29]. DFUs will be assessed at three time points: pre-intervention (baseline), after 5 weeks (10 sessions), and after 10 weeks (20 sessions). The calculation of the reduction rate will follow the same parameters used by Ahmed and Irfan [30], represented by the formula: $$\:\frac{Af-Ai}{Ai}\:x\:100$$. Here, Ai and Af denote the initial and final ulcer areas, respectively. Ulcer area measurements will be performed by a blinded independent evaluator, who will be unaware of group allocation. The primary outcome will be compared between groups and across time points using repeated-measures analysis.

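### Ulcer duration is recorded for every participant, but no group comparison adjusts for it, so available precision is given up and chance imbalance goes uncorrected

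*Protocol article*

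**What the plan says.** Eligibility criteria admits people "aged 18 years or older, with a medical diagnosis of type 2 diabetes and diabetic ulcers located on the lower limbs". The exclusions begin with "Volunteers presenting signs of infection, osteomyelitis, ischemia, inability to attend the scheduled number of sessions, use of advanced ointments or dressings" and go on to contraindications. Neither list refers to the age of the ulcer.

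Initial assessment has the evaluator record "time since DM diagnosis, and ulcer duration" on a form completed for each participant.

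Randomization, allocation, and blinding says that "Participants will be assigned to one of three groups through an online randomization program" and names no stratification factor.

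Ulcer reduction rate fixes the measurement times: "DFUs will be assessed at three time points: pre-intervention (baseline), after 5 weeks (10 sessions), and after 10 weeks (20 sessions"). It promises a repeated-measures comparison between groups and over time, with no covariate named.

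Statistical analysis assigns one-way ANOVA or Kruskal–Wallis to group differences, chi-square to categorical data, and one-way repeated-measures ANOVA or Friedman to within-group change. On baseline data it says only that "Sociodemographic data will be presented as descriptive statistics". Ulcer duration appears in none of these comparisons, nor in the responder analysis.

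**The concern.** How long an ulcer has been open is a plausible predictor of how much it will shrink in 10 weeks. With no limit on ulcer age, the sample may run from recent ulcers to long-standing ones. If duration is prognostic, two things follow for an unadjusted comparison. Variation in outcome that duration could explain stays in the error term, which widens confidence intervals and lowers power. And if one arm happens to receive more recent ulcers, the estimated difference carries that imbalance with nothing to correct it.

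The variable needed to deal with both is already on the baseline form. The time to commit to it is before the data are seen, because an adjustment chosen after unblinding is much less credible.

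**Working it through.** **The plan's own figure.** Sample size gives f = 0.31, alpha 0.05, power 0.90, three groups, three time points and N = 93. Assuming a correlation of 0.5 between time points (not stated), the between-groups test of a repeated-measures ANOVA has

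λ = f² × N × m / (1 + (m − 1)ρ) = 0.0961 × 93 × 3 / 2 = 13.41, with 2 and 90 df.

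Power is 0.907, and 93 is the smallest multiple of three that reaches 0.90. The section names the interaction test, which gives a different N (30) at that correlation with sphericity. That is a separate matter; here the between-groups test serves only as a baseline for measuring gain.

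**Precision.** The documents give no correlation r between (log) duration and outcome, so a range is assumed. Adjustment leaves residual variance 1 − R², with R² = r². The gain in effective patients is 1/(1 − R²). For power, f is divided by √(1 − R²). This is approximate, since it treats the reduction as equal at all time points.

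| Assumed r | R² | Residual variance | Gain in effective N | 93 patients act like | Approx. power at N = 93 |
|---|---|---|---|---|---|
| 0 | 0 | 1.00 | 0% | 93 | 0.907 |
| 0.10 | 0.01 | 0.99 | 1% | 94 | 0.910 |
| 0.20 | 0.04 | 0.96 | 4% | 97 | 0.919 |
| 0.32 | 0.10 | 0.90 | 11% | 103 | 0.935 |
| 0.45 | 0.20 | 0.80 | 25% | 116 | 0.959 |

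**Cost of the covariate.** Taking the error df from 90 to 89 at R² = 0 leaves power at 0.907. If duration proves unrelated to outcome, essentially nothing is lost.

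**Chance imbalance.** With 34 per arm and no stratification, the difference in mean duration between two arms, in SD units, has standard deviation √(2/34) = 0.24. It exceeds 0.25 SD in about 30% of trials and 0.5 SD in about 4%, for a given pair of arms.

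As an illustration, assume that 40% of ulcers are recent. The standard error of the difference in that share is √(2 × 0.4 × 0.6/34) = 0.119, or 11.9 percentage points. A gap of 15 points or more then has probability 0.21 by the normal approximation (z = 0.15/0.119 = 1.26). Counted exactly, such a gap needs at least 6 patients of 34, and the probability is 0.17, about one trial in six per pair.

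**What that imbalance does to the result.** A 15-point gap shifts the arm difference by 0.15 × √(R²/0.24) outcome SDs:

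- R² = 0.10: 0.10 SD
- R² = 0.20: 0.14 SD

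Against an unadjusted standard error of √(2/34) = 0.24 SD, that is about 0.4 to 0.6 of one standard error. It could move a borderline result but would not create a large effect by itself.

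**The case against.** **Covariates belong in the SAP.** An article need not list them, and silence would be no finding. But Statistical analysis is not silent: it names the between-group tests, and as named these take no covariate. The repeated-measures comparison under Ulcer reduction rate could carry one, so part of this objection stands. The article does not rule adjustment out for the primary outcome; it just does not provide for it.

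**Randomisation already handles this.** This stands as far as bias is concerned. A reader might infer that, with no run-in and no untreated arm, nothing separates natural healing from treatment. For the between-arm contrast that is wrong. Natural healing acts in all three arms, allocation is random, and the control is concurrent. Chance imbalance is also allowed for in the p-value and confidence interval of an unadjusted test. What remains is precision, and the credibility of the particular result obtained.

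**Eligibility does not match the rationale.** A reader might take the keywords ("Diabetic foot ulcer, Chronic wounds, Low-level laser therapy, Phytotherapy, Ulcer healing") together with the Introduction's remarks on prolonged inflammation to mean that recent ulcers should be excluded, or a run-in added. The documents do not support calling this an error. The declared population is non-infected diabetic ulcers, and the criteria fit it. A narrower population is a design preference.

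**The gain may be trivial.** This stands as a possibility. At r of 0.1 to 0.2 it is 1% to 4%. The source of f = 0.31 is not at hand and may already reflect ulcers of mixed age, so it cannot be said that the trial is underpowered on this account.

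**Duration may be tabulated at baseline.** It may. The point is that no comparison uses it.

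**Conclusion.** The point holds as an inexpensive improvement in precision. A plausible prognostic factor is collected from everyone, ulcers of any age are eligible, and the comparisons as written do not use it. The benefit depends on an assumed correlation: about 1% to 4% more effective patients at r of 0.1 to 0.2, and 11% to 25% more at R² of 0.10 to 0.20 (103 to 116 from 93). These figures are for a linear model of the area outcome and do not transfer directly to the responder analysis.

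Two stronger conclusions are not supported. The unadjusted comparison is not systematically biased. Nor would an adjusted result license a claim about chronic ulcers: a main-effect covariate yields one treatment effect across all durations, and a claim specific to chronic ulcers would need a duration-by-treatment interaction or a subgroup analysis.

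**What to change.** Keep eligibility, sample size and visits as they are. In Statistical analysis:

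1. Primary outcome: replace the unadjusted between-group test with a repeated-measures or ANCOVA model with group as a factor and log ulcer duration from the baseline form as a pre-specified covariate.
2. The 50% responder outcome: use a logistic model with group and log ulcer duration. Averaging its predicted risks over the sample keeps the comparison on the absolute scale that the planned ARR and NNT require.
3. Optional, if allocation has not begun: stratify by shorter versus longer duration at a pre-stated cut-off and keep duration in the model. This needs a separate allocation sequence and envelope set per stratum. If allocation has begun, the covariate alone is enough.

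The cost is a few sentences and about one degree of freedom, with no extra patients, visits or measurements. The change should be dated before any unblinded data are seen.
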